## Methods/Design

### Sponsor

The Mukoviszidose Institut gGmbH is the sponsor for this trial. Collaborators are Novo Nordisk, Mucoviscidose-ABCF2, Vaincre la Mucoviscidose and Assistance Publique - Hôpitaux de Paris. The protocol and all trial documents have been approved by the ethic committees responsible for the respective trial sites. The first vote was received from the ethical committee of the MHH Hannover (22.08.2001, No. 2739). The responsible competent authorities gave approval (so far applicable) under EudraCT Number 2006-001254-27 [for France and Italy], BfArM Number 4019636 [for Germany] and BMSG Number 21.405/219 [for Austria]. The trial was public registered under ClinicalTrials.gov Identifier NCT00662714.

### Eligibility criteria

Informed consent was to be obtained before any trial-related activities. CF was diagnosed by positive sweat test and/or two disease-causing Cystic Fibrosis Transmembrane Conductance Regulator (CFTR) mutations. Patients had diagnosed diabetes mellitus by OGTT done less than six months before (one year before in Italy). The subjects were over 10 years of age (12 years in France and Italy). Diabetes was confirmed by a second OGTT test. Patients in France needed in addition fasting blood glucose levels ≤170 mg/dl. Patients have been excluded with diagnosis of type 1 diabetes or diabetic keto-acidosis (blood glucose > 350 mg/dl and arterial pH < 7.25). Already treated diabetes mellitus by oral antidiabetic medication or insulin led to exclusion of these patients. Severe pulmonary insufficiency with FEV1 < 25% (France and Italy) or < 40% (Germany and Austria), participation in another clinical trial less than one month before inclusion in this trial, severe liver insufficiency or PEG/gastric tube/total parenteral nutrition for more than 4 weeks were not at inclusion. Patients must not be pregnant and in France and Italy breast-feeding or the intention of becoming pregnant or not using adequate contraceptive measures were not allowed. Patients after transplantation or in France patients which have been planned for transplantation could not be included. For Germany subjects receiving concomitant medication known to interfere with repaglinide therapy were not included. In France and Italy proliferative retinopathy, type 2 diabetes, severe renal insufficiency, history of alcoholism, drug abuse, psychiatric disease or personality disorders likely to invalidate voluntary consent or to prevent good compliance with the trial protocol, legal incapacity or limited legal capacity, known or suspected allergy to the insulin or any compositional component, known or suspected allergy to repaglinide or receiving concomitant medication known to interfere with glucose metabolism prevented inclusion in this trial.

### Trial conduct

In all CF-patients 10 years or older, an oral glucose tolerance test (OGTT) following standard WHO recommendations has be performed. Oral medication was postponed until after the test, however, inhalation therapy could be performed prior to the test. During acute infections or exacerbations of a chronic infection, the test was postponed for 3 to 4 weeks until acute symptoms improved. OGTT were classified as normal glucose tolerance, impaired glucose tolerance/impaired fasting glucose or diabetes mellitus according to the WHO cut off values [6].

### Randomization

After detailed information by the physicians of the local CF centre, the patient or legal guardian decided to give written informed consent to participate in the study. The trial was open-labelled in order to avoid use of double-dummy technique which would have required an unacceptable increase in the number of injections for the patients. The patients were allocated to the treatment regimen according to a randomisation list generated by a geigy random number table by central fax randomisation. Stratification was conducted according to gender and two age groups (10–15 years, >15 years). Every randomised patient should have been observed for at least 2 years and be included in the final analysis (“intention-to-treat” analysis).

The trial procedures are summarised in the following Table 1.

**Table 1 T1:** Trial procedures

**Visits/months**	**VS**	**V1**	**V2**	**V3**	**V4**	**V5**	**V6**	**V7**	**V8**	**V9**	**End**
		**0**	**3**	**6**	**9**	**12**	**15**	**18**	**21**	**24**	
Informed consent	+										
Selection/exclusion criteria	+										
Randomisation		+									
Inclusion/exclusion criteria		+									
Demographic data	+										
Medical history	+										
Physical examination	+	+	+	+	+	+	+	+	+	+	+
Concomitant illness and medication	+	+	+	+	+	+	+	+	+	+	+
Blood glucose profile			+	+	+	+	+	+	+	+	+
HbA_1c_		+	+	+	+	+	+	+	+	+	+
Pulmonary function		+	+	+	+	+	+	+	+	+	+
IV therapy (antibiotics)		+	+	+	+	+	+	+	+	+	+
Adverse events		+	+	+	+	+	+	+	+	+	+
Hypoglycaemic episodes			+	+	+	+	+	+	+	+	+
Drug dispensation		+	+	+	+	+	+	+	+		

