**Methods/Design:**

In all cystic fibrosis patients with an age of 10 years or older, an oral glucose tolerance test is recommended. The result of this test is classified according to the WHO cut off values. It is required to have two diabetes positive oral glucose tolerance tests for the diagnosis of diabetes mellitus.

This study is a multi-national, multicentre, open labelled, randomized and prospective controlled parallel group’s trial, with 24 months treatment.

The primary objective of this trial is to compare the glycaemic control of oral therapy with Repaglinide with insulin injections in patients with cystic fibrosis related diabetes after 2 years of treatment.

The trial should include 74 subjects showing cystic fibrosis related diabetes newly diagnosed by oral glucose tolerance test during annual screening for cystic fibrosis related diabetes.

Patients are randomised by central fax randomisation.

Primary endpoint is mean HbA1c after 24 months of treatment. Secondary endpoints are change in FEV1% predicted and change in BMI-Z-score.

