### Outcome measures

Primary endpoint:

Primary endpoint was the change in HbA1c after 24 months of treatment.

Secondary endpoints:

Secondary endpoints were glycaemic control assessed by mean HbA1C and mean blood glucose profile; change in BMI-Z-score; change in FEV1% predicted and safety assessed by antibiotic therapy, incidence of adverse events, number of hypoglycaemic episodes, all symptomatic hypoglycaemia, hypoglycaemia that necessitates the help of other persons, hypoglycaemia with unconsciousness or coma and number of blood glucose levels below 50 mg/dl in relation to all blood glucose measurements.

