### Power calculation/analysis

Which number of patients was necessary to show a significant difference between therapy strains of 80% power on the one hand and p <0.05 on the other? Retrospective HbA1c data from a database of the CF centre at Medical School Hannover were used. Measurements of n = 132 HbA1c within the first two years after diabetes diagnosis of n = 44 patients older than 10 years at the date of diagnosis resulted in an average value of HbA1c = 5.6 ± 1.5 (average value ± SD). Within a similar group (older than 10 years) but without diabetes n = 763 measurements yielded an HbA1c of 4.6 ± 0.68 (average value ± SD). A difference of 1 (which is in the range of individual variations during treatment especially in youngsters and young adults) between therapy groups was considered relevant [12]. Calculation with *n Query®* of necessary patients for each group was done with these parameters: Two group *t*-test of equal means (equal n’s) 1; Test significance level, α 0,050; 2 sided test; Group 1 mean, μ_1_ 5,600; Group 2 mean, μ_2_ 4,760; Difference in means, μ_1_ - μ_2_ 1,000; Common standard deviation, σ 1,500; Effect size, δ = |μ_1_ - μ_2_|/σ 0,667; Power 80%. Based on the above assumptions the number of patients in each group was calculated as n = 37. Over a treatment time of 2 years, about 30% of patients were assumed to drop out of the study. Therefore, n = 111 patients have been necessary at the beginning of the study to ensure a number of n = 74 remaining patients at the end of the study.

For analysis, the differences of primary parameter HbA1c repeated measures-ANOVA will be applied. The one-sided zero hypothesis (Repaglinide is not worse than insulin) will be dismissed if a p value under 0.05 occurs. The two therapy groups will be compared concerning secondary parameters statistically using the fisher exact test (comparison of discrete events), the Wilcoxon (non-parametrically distributed parameters) and the *t*-test (parametrically distributed parameters). For comparison of drop-outs between the treatment stains a Cox proportional-hazard-ratio model will be applied.

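### Randomisation is stratified by gender and age group, but the named analyses include neither these factors nor baseline as a covariate; baseline enters only through change scores, which likely costs precision

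*Protocol article*

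**What the plan says.** Under Randomization, the protocol article says "Stratification was conducted according to gender and two age groups", the age groups being 10–15 and >15 years. Table 1 in the same section schedules HbA1c and pulmonary function at V1 (month 0). BMI has no row of its own and would presumably come from the physical examination, also done at V1.

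Under Outcome measures, "Primary endpoint was the change in HbA1c after 24 months of treatment", and the secondary endpoints include "change in BMI-Z-score; change in FEV1% predicted". The abstract words the primary endpoint differently: "Primary endpoint is mean HbA1c after 24 months of treatment".

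Under Power calculation/analysis, the text on the primary parameter is that for "the differences of primary parameter HbA1c repeated measures-ANOVA will be applied". No model terms are listed. For the rest, "The two therapy groups will be compared concerning secondary parameters statistically using the fisher exact test" for discrete events, Wilcoxon for non-parametric parameters and the t-test for parametric ones. A Cox model is named for drop-outs. None of these analyses is said to include gender, age group or a baseline value.

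**The concern.** Stratified randomisation balances the arms on the stratifying factors. If those factors predict the outcome and the analysis leaves them out, their variance stays in the error term. The standard error is then too large for the design, and the test is conservative.

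A separate loss concerns baseline. Subtracting the baseline value fixes its coefficient at 1, whereas ANCOVA estimates it. With equal variances at the two times, the change score is less precise than ANCOVA whenever the correlation is below 1. It is less precise even than ignoring baseline when the correlation is below 0.5.

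For the parametric secondary endpoints this goes beyond detail left to another document. A two-sample t-test is positively named, and as named it cannot carry a stratum or a covariate. With 37 patients per group planned, precision is worth protecting, and the variables needed are already scheduled for collection.

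**Working it through.** **Inputs from Power calculation/analysis:** two-sided α = 0.05, power 80%, difference 1.0, SD 1.5, equal groups, 37 per group. The SD comes from retrospective single HbA1c values (132 measurements in 44 patients). It is neither the SD of a change nor a baseline-adjusted SD.

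**Inputs not in the documents, hence assumed:** the correlation r between baseline and 24-month HbA1c (0.3, 0.5, 0.7), equal variances at both times, and the share R² of outcome variance explained by gender and age group (2%, 5%, 10%).

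**Step 1: the plan's own figure.** The exact two-sample t-test calculation with 1.0/1.5 = 0.667 gives 36.31, so 37 per group, with power 80.8%. The stated 37 reproduces. It describes an unadjusted comparison of raw HbA1c values.

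**Step 2: SD under each use of baseline.**
- Raw 24-month value: 1.5
- Change score: 1.5 × √(2(1 − r))
- ANCOVA residual: 1.5 × √(1 − r²)

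For example, at r = 0.3 the change SD is 1.5 × √1.4 = 1.77 and the ANCOVA SD is 1.5 × √0.91 = 1.43.

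**Step 3: power and precision at 37 per group.** The 95% half-width is t(0.975; 72) × SD × √(2/37) = 1.993 × SD × 0.2325. It serves only as a measure of precision.

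| r | Analysis | SD | Power | Half-width |
|---|---|---|---|---|
| any | raw 24-month value | 1.50 | 81% | 0.695 |
| 0.3 | change score | 1.77 | 67% | 0.823 |
| 0.3 | ANCOVA | 1.43 | 84% | 0.663 |
| 0.5 | change score | 1.50 | 81% | 0.695 |
| 0.5 | ANCOVA | 1.30 | 90% | 0.602 |
| 0.7 | change score | 1.16 | 95.5% | 0.539 |
| 0.7 | ANCOVA | 1.07 | 98% | 0.496 |

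The ratio of change-score to ANCOVA width is √(2/(1 + r)), so the change-score interval is 24%, 15% and 8% wider at r = 0.3, 0.5 and 0.7. Spending three degrees of freedom on baseline, gender and age group (69 instead of 72) moves the critical value from 1.993 to 1.995. The ANCOVA powers stay at 84%, 90% and 98%.

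**Step 4: ignoring the strata alone.** The width ratio is 1/√(1 − R²). The actual level of a nominal 5% test is about 2Φ(−1.96/√(1 − R²)).
- R² = 2%: 1% wider, level 4.8%
- R² = 5%: 3% wider, level 4.4%
- R² = 10%: 5% wider, level 3.9%
- R² = 0: no loss

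**The case against.** The strongest reply is that a condensed article has been silent, not that it has excluded anything. The primary analysis gets one clause, with no terms listed, and both a repeated-measures ANOVA and a Cox model can carry gender, age group and baseline. A fuller protocol or SAP may specify them. This stands for HbA1c, where the point is only that no covariate is stated. It does not stand for the t-test, which is the method the article fixes and which has no place for a covariate.

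A reader might infer that the plan makes no use of the baseline measurements at all. The documents do not support that. Three endpoints are defined as changes, and the repeated-measures ANOVA may also include month 0. Baseline would be absent only if the abstract's mean HbA1c at 24 months, analysed without the month-0 value, were the operative endpoint.

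A reader might also set 84%, 90% and 98% against the 81% for the raw value and read the difference as the gain. Since the endpoint is a change, the change score is the fairer comparator. The gain is then about 2 points at r = 0.7, but about 17 at r = 0.3. None of these figures models the full series of visits.

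Three further replies stand. An unadjusted test after stratified randomisation is conservative, not invalid. The sample size does not rely on adjustment. The article plans a decision by p-value and specifies no confidence interval, so it cannot be said that the trial's answer depends on the width of one.

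**Conclusion.** The point holds as one of efficiency. The named analyses include neither the stratification factors nor baseline as a covariate, and the t-test cannot include them.

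The larger part of the likely loss comes from using change scores. Relative to ANCOVA it is about 17, 10 and 2 points of power at assumed r of 0.3, 0.5 and 0.7. Below r = 0.5, the change score's power drops under that of the raw 24-month value on which the trial was sized. The loss from ignoring the strata is small over the assumed 2% to 10% of variance, and nil if they do not predict the outcome.

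The sizes rest on assumed r and R², on equal variances, and on a two-time-point comparison at the planned SD of 1.5. The documents give neither r nor R², so the actual loss cannot be fixed. This is an improvement the sponsor should make; it does not show bias or an inflated error rate.

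**What to change.** - **Primary HbA1c model:** include baseline HbA1c, gender and age group (10–15, >15 years) as covariates. With baseline in a linear model, the 24-month value and the change from baseline give the same treatment contrast at that visit, so the model serves either endpoint wording. The two wordings still need to be reconciled.
- **FEV1% predicted and BMI-Z-score:** replace the t-test on change by ANCOVA with the baseline value and the same two strata.
- **Cost:** about three degrees of freedom and no new data, as the variables are scheduled at entry (BMI through the physical examination).
- **Timing:** Trial status says analysis is ongoing, and the trial is open-label. Fix the model in a dated document before any treatment comparison is seen. If that is no longer possible, keep the stated analysis and report the adjusted one as additional.

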### Therapy duration

Patients in both therapy strains hade to be monitored for 2 years; every 3 months, a standardised examination and documentation was intended.

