### Discontinuation criteria

The therapy in one of the therapy strains should have been considered ineffective if one of the following discontinuation criteria had been met: No acceptable metabolic control obtainable over a time span of 3 months regardless of dose adjustment according to protocol and therapy compliance; occurrence of non-tolerable undesired side effects under therapy; transaminase increase to 3 times the initial value; non tolerable allergic reactions; discontinuation of study by patient/family; se of systemic steroids necessary; desired or occurring pregnancy; PEG/nasal tube feeding/completely parental alimentation of at least 4 successive weeks or transplantation.

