### Therapy alternatives when reaching discontinuation criterion

a. Insufficient metabolism control during therapy with repaglinide.

Generally, a shift to insulin would have been necessary; doses of 3 injections of regular insulin before meals were recommended. If fasting blood glucose levels had been high, an additional dose of intermediate/long-lasting insulin before going to sleep was advisable. A shift from repaglinide to glibenclamide would have make sense only if allergic reactions to repaglinide occurred. The use of other oral anti-diabetics could not be recommended based on current scientific knowledge.

b. Insufficient metabolic/glycaemic control during therapy with three injections of regular insulin.

Usually a standard intensified therapy of 4–5 injections a day was recommended.

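### Intention to treat is stated, but the planned HbA1c analysis may lose treatment failures or count them on the comparator, which can shrink the difference in a trial asking whether repaglinide matches insulin

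*Protocol article*

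**What the plan says.** All references are to the protocol article.

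- **Randomization** sets an intention-to-treat rule: "Every randomised patient should have been observed for at least 2 years and be included in the final analysis". **Therapy duration** agrees with it: "Patients in both therapy strains hade to be monitored for 2 years".
- **Power calculation/analysis** assumes about 30% drop-out over two years and plans 111 patients at the start so that 74 remain at the end. For analysis it says: "the differences of primary parameter HbA1c repeated measures-ANOVA will be applied". The one-sided null is that repaglinide is not worse than insulin, with rejection at p below 0.05. A Cox model is planned to compare drop-outs between arms.
- **Discontinuation criteria** begins its list of grounds for calling a therapy ineffective with "No acceptable metabolic control obtainable over a time span of 3 months regardless of dose adjustment". The same list contains "discontinuation of study by patient/family".
- **Therapy alternatives when reaching discontinuation criterion** says of insufficient control on repaglinide: "Generally, a shift to insulin would have been necessary". For insufficient control on insulin: "Usually a standard intensified therapy of 4–5 injections a day was recommended".

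**The concern.** The primary endpoint is HbA1c at 24 months, and the first reason for stopping assigned treatment is poor glycaemic control. Stopping can therefore be related to the outcome. The list of criteria also merges two different events, stopping the assigned drug and leaving the study, so a reader cannot tell which patients still supply HbA1c.

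A repaglinide failure can then affect the primary comparison in two ways. The patient may leave, and a repeated-measures ANOVA in its classical form would discard the incomplete record. Or the patient may stay under the intention-to-treat rule and be measured at month 24 on insulin, the comparator. Insulin failures are also treated further, but they remain on insulin, so crossing to the other arm's drug class runs in one direction.

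This matters because of the question asked. The Background section asks whether repaglinide is as effective as insulin, and the stated null is that it is not worse. A smaller observed difference makes that null harder to reject, and non-rejection could be read as the favourable result. In such a trial, intention to treat is not automatically the cautious choice.

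**Working it through.** **1. The plan's own figures.** Inputs from Power calculation/analysis: difference 1.0, SD 1.5, two-sided alpha 0.05, power 80%, equal groups. Power comes from the noncentral t distribution with 2n − 2 degrees of freedom and noncentrality d / (SD × √(2/n)). At n = 37 the noncentrality is 1 / (1.5 × √(2/37)) = 2.87 and power is 80.8%; at n = 36 power is 79.7%. So 37 per group, 74 in all, reproduces. The starting number does not reproduce at exactly 30%: 74 / 0.70 = 105.7, that is 106, whereas 111 = 74 / (2/3), a loss of one third.

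**2. Failures kept and measured on insulin.** The documents give no switch rate, so a share f of 10–30% of the repaglinide arm is assumed. Switchers are assumed to have the insulin-arm mean at month 24. The observed difference is then (1 − f) × 1.0. If switchers are kept, all 111 are followed, about 55 per group.

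| Assumed f | Difference | Two-sided power, 55 per group | Patients per group for 80% power |
|---|---|---|---|
| 0% | 1.0 | 93% | 37 |
| 10% | 0.9 | 88% | 45 |
| 20% | 0.8 | 79% | 57 |
| 30% | 0.7 | 68% | 74 |

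**3. Failures lost.** Assume month-24 means of 6.6 (repaglinide) and 5.6 (insulin), SD 1.5, with every patient above a common cut c missing. The mean of those remaining is μ − σ × φ(a)/Φ(a), where a = (c − μ)/σ. For c = 7.0:

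- Repaglinide: a = 0.267, mean 6.6 − 0.95 = 5.65.
- Insulin: a = 0.933, mean 5.6 − 0.47 = 5.13.
- Difference 0.52.

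| Cut | Lost, repaglinide | Lost, insulin | Completer difference |
|---|---|---|---|
| 7.0 | 39% | 18% | 0.52 |
| 7.5 | 27% | 10% | 0.61 |
| 8.5 | 10% | 3% | 0.80 |

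The cut of 7.0 loses about 29% overall, close to the plan's 30%.

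**4. How far step 3 depends on the link to HbA1c.** Removing patients on the outcome value itself is the extreme case. If the variable driving drop-out has a within-arm correlation of only 0.5 with month-24 HbA1c, the cut of 7.0 gives 0.76 instead of 0.52. With correlation 0 the difference stays at 1.0: there is no bias, even though the arms lose different proportions.

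**The case against.** Several points on the other side stand.

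- **Complete-case deletion is not stated.** A reader might infer that incomplete patients are dropped. The article names only a repeated-measures ANOVA, and missing-data rules may sit in a full protocol or analysis plan that is not shown.
- **Sizing on 74 remaining patients is a routine allowance for lost data.** A reader might infer that only those 74 are analysed. The article does not say so; its only statement on who is analysed is the intention-to-treat rule.
- **Counting values after a switch follows from intention to treat.** It answers whether starting on repaglinide, with insulin if needed, does as well as starting on insulin. It misleads only if the question is control on repaglinide itself. The Primary objective, which compares control on each therapy, leans that way, but the article does not settle it.
- **The direction is not established.** A reader might infer that the comparison must be biased in favour of repaglinide. Failure rates by arm are not given, insulin failures are also intensified, and many listed criteria (allergy, steroids, pregnancy, transplantation) are not defined by glycaemia.
- **The power loss is easily overstated.** Combining 30% switching with 37 per group gives 51%. That keeps the switchers while using the number left after drop-out. With switchers retained, about 55 per group is the matching figure and power is 68%.

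The planned Cox comparison would show differential drop-out, but the article does not connect it to the HbA1c analysis. It therefore does not remove the problem. Nor do the other points: the stated method sits poorly with the stated population, and failures on one arm generally take up the other arm's drug class.

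**Conclusion.** The concern holds in a conditional form. The article promises an analysis of everyone randomised, expects substantial drop-out, and names a method that in its classical form cannot use incomplete patients. It also merges treatment failure with leaving the study and generally moves repaglinide failures to the comparator.

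If failure is commoner on repaglinide, or loss is tied to high HbA1c, the HbA1c difference shrinks in the direction that supports repaglinide. Under the assumptions above, a true difference of 1.0 becomes 0.9–0.7 when 10–30% switch and are kept, and 0.52–0.80 when failures are lost at cuts of 7.0–8.5. The second range is less severe if drop-out is only partly related to HbA1c. Switch rates, cuts and the 6.6 mean are illustrative and not from the documents. The text supports neither a certain bias nor a claim that failures are excluded.

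**What to change.** 1. Make the primary analysis a likelihood-based mixed model for HbA1c in all randomised patients, using every available value, including those after assigned treatment is stopped. State the sample size for that same population.
2. Record stopping assigned treatment separately from leaving the study, with dates for each, and state whether HbA1c continues to be collected and counted after a discontinuation criterion is met.
3. Add a prespecified supportive analysis that does not use HbA1c after a switch as evidence for repaglinide. One option is to set values after a change of drug class to missing and impute them from the patient's pre-switch course, with a sensitivity analysis assuming worse control after failure.
4. Interpret a conclusion that repaglinide is as effective only in the light of both analyses.

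The cost is a changed model, one further analysis, and discontinuation and switch dates from the case report forms. The supportive analysis will have a wider interval. The Trial status section says analysis is ongoing, so these choices should be fixed before results by arm are examined. No change to any treatment rule is proposed.
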